### Follow up surveys

#### Follow-up for ITN hang-up and adverse events

Between 1 week and up to 1 month post-distribution, sleeping places in houses in the net sampling lists (cohort 1 and cohort 2) will be observed to ensure that study nets have been set up. Where necessary, study teams will assist participants in hanging up their nets. The nets available in the house will also be checked to ensure that they match with what is available in the net sampling list which was generated after distribution and corrections will be made as necessary. During these visits, householders will be encouraged to use the study nets over any other nets available with them. Using a questionnaire, the adverse effects related to net usage will be investigated in 30 randomly selected households in each study arm at each study site. Heads of households will be questioned on any perceived adverse events including sneezing, itching, headache, numbness, eye discharge, any unpleasant smells and nausea in line with WHO guidelines. Participants will be advised to seek medical care from the nearest health facility should the symptoms persist.

#### Follow-up for ITN attrition

Net attrition rate in households will be measured by recording the physical presence of the net at 6-, 12-, 24- and 36-months post ITN distribution. All households in cohort 1 will be visited and nets assessed for attrition at each timepoint by recording the physical presence/absence of each net attributed to the household. Where a net is not found, the householder will be questioned about the reason for the loss of the net e.g. given away, sold, stolen, worn out and disposed of etc. Any study nets which have never been used, will be recorded and excluded from the analysis. ITNs lost due to wear and tear will be considered as lost due to attrition, and those lost because they were stolen, sold or given away to others, will be considered as lost to follow-up. During these surveys, a questionnaire adapted from WHO guidelines will be used to collect data on the number of washes and washing practices for the nets found in each household. The household surveys will be conducted by an experienced socio-anthropologists.

#### Follow-up for ITN fabric integrity

Fabric integrity (hole index) and condition will be observed on all nets of cohort 1 at 6-, 12-, 24- and 36-months post distribution. Where the minimum number (250) of nets for fabric integrity is not attainable from the longitudinal cohort (cohort 1) due to loss, ITNs sampled destructively from the same clusters for bio-efficacy would first be examined for fabric integrity prior to the bio-efficacy studies. The survey team will inspect the nets outside in broad day light to determine the hole index using a portable frame over which the net can be draped during inspection. The nets will be returned to the family right after the inspection. Hole number and size will be assessed on each ITN panel using hole assessment sheet and classified into 4 sizes (size 1: 0.5-2 cm, Size 2: 2–10 cm, Size 3: 10-25 cm, and size 4: > 25 cm). Physical integrity will be measured as the proportionate hole index (pHI), categorized based on recommended cut-off points into “good” condition (pHI 0–64), “acceptable” condition (pHI 65–642) and “torn” (pHI 643 +).

### Bioefficacy studies and chemical analysis

A separate subsample of nets belonging to cohort 2 will be randomly selected per arm for bioefficacy studies and chemical analysis. Nets of each type (DuraNet® Plus and DuraNet®) will be destructively sampled from households at 6, 12, 18-, 24-, 30- and 36-months post-distribution and replaced with new nets of the same type (brand) at each sampling point. They will be subjected to chemical analysis to monitor alphacypermethrin and PBO content and to laboratory bioassays (WHO cone bioassays and tunnel tests where necessary) and experimental hut trials to monitor entomological efficacy against mosquito vectors over time. For laboratory bioassays, net pieces measuring 30cmx30cm will be cut from each net following WHO guidelines [9]. The number of whole ITNs of each type to be subjected to each type of study at each timepoint is summarised in Table 2 below.

**Table 2 Tab2:** Number of DuraNet® Plus and DuraNet® ITNs to be sampled for laboratory assays, chemical analysis and hut trials at each study site

Months post ITN distribution	No of ITNs for Laboratory assays	No. of pieces per ITN	Total number of pieces for bioassays	No. of pieces for chemical analysis^a^	ITNs for hut trials^b^
0	30	5	150	150	-
6	30	4	120	-	-
12	30	4	120	120	54
18	30	4	120	-	-
24	30	4	120	120	54
30	30	4	120	-	-
36	50	4	200	200	54
**Total**	**230**		**950**	**590**	**162**

^a^ Net piece preserved for chemical analysis will be obtained from adjacent positions on the same ITNs cut for bioassays. These net pieces would measure 30cmX30cm

^b^The hut trials will be performed only in Benin but will include nets from all study sites

#### Chemical analysis

The net pieces preserved for chemical analysis at 0, 12, 24 and 36 months (590 pieces per net type) will be wrapped in Aluminum foil and stored at 4^0^c (± 2°c) and afterwards shipped for chemical content analysis to International Institute of Biotechnology and Toxicology (IIBAT), a GLP laboratory in India for detection of alphacypermethrin and PBO content using high performance liquid chromatography. Net pieces will be shipped within 3 months after collection.

#### WHO cone bioassays and tunnel tests

Cone bioassays and tunnel tests will be performed at research partner institutions in each study country (Centre de Recherche Entomologique de Cotonou in Benin, Centre for Research in Infectious Diseases, Cameroon, and Vector Control Training Centre in Tanzania). To monitor the bioefficacy of alphacypermethrin in DuraNet® Plus and DuraNet®, ITN pieces obtained from each field collected net will be tested in standard WHO cone bioassays. One hundred (100) unfed 3–5 days old mosquitoes of the susceptible *Anopheles gambiae* Kisumu strain will be exposed for 3 min to each ITN in replicates of 5 mosquitoes per cone and 2 cones per net piece. Knockdown will be recorded after 60 min and mortality rates after 24 h. Comparison will be made to a new unused net of each ITN type. ITNs which fail to achieve WHO efficacy criteria in cone bioassays (pooled knock-down is ≥ 95% and/or pooled 24 h mortality is ≥ 80%) will be subjected to tunnel tests. For tunnel tests, 100 unfed 5–8 days old susceptible Kisumu mosquitoes will be exposed overnight to one ITN piece from each failed net and mortality (after 24 h) and blood-feeding inhibition rates measured following standard WHO protocols. The proportion of ITNs of each type passing criteria for alpha-cypermethrin bioefficacy in cone bioassays (≥ 95% knockdown or ≥ 80% mortality) and/or tunnel tests (≥ 80% mortality or ≥ 90% blood-feeding inhibition) will be determined for each study site. All cone bioassays will be performed at 27 ± 2 °C and 75% ± 10%

To monitor the bioefficacy of PBO in DuraNet® Plus, tunnel tests will be performed using 1 net piece from ITNs withdrawn for bioassays at 12, 24 and 36 months using the pyrethroid resistant *An. coluzzi* Akron strain (BEI resources) for Benin and Cameroon and the pyrethroid resistant *An gambiae ss* Zenet strain in Tanzania. Both strains exhibit intense resistance to pyrethroids mediated by high kdr frequencies and overexpressed P450 enzymes evidenced by increased mortality with alpha-cypermethrin following PBO pre-exposure in susceptibility bioassays. They will be fully characterised prior to each round of laboratory bioassays. The proportion of DuraNet® Plus ITNs inducing ≥ 80% mortality of the pyrethroid resistant strain in tunnel tests will also be determined for each study site. Comparison will be made with a new unused DuraNet® Plus at each timepoint. All tunnel tests will run overnight between 18:00 and 09:00 at 27 ± 2 °C and 75% ± 10% relative humidity.

#### Experimental hut trials

To further assess the entomological superiority of DuraNet® Plus over DuraNet®, experimental hut trials will be performed with field collected ITNs at 12-, 24- and 36-months post ITN distribution from each country at the Cove experimental hut station in Benin against wild free-flying pyrethroid-resistant *Anopheles gambiae* sl. Fifty-four (54) DuraNet® Plus and 54 DuraNet® nets from all three countries will be tested together in experimental huts at each annual timepoint. Comparison will be made with new unused nets of each type. The hut trials will consist of the following 9 treatments:Untreated net – 6 replicatesDuraNet® (new unused) – 6 replicatesDuraNet® Plus (new unused) – 6 replicatesDuraNet® Benin (12-, 24- or 36-months field net) – 54 replicatesDuraNet® Cameroon (12-, 24- or 36-months field net) – 54 replicatesDuraNet® Tanzania (12-, 24- or 36-months field net) – 54 replicatesDuraNet® Plus Benin (12-, 24- or 36-months field net) – 54 replicatesDuraNet® Plus Cameroon (12-, 24- or 36-months field net) – 54 replicatesDuraNet® Plus Tanzania (12-, 24- or 36-months field net) – 54 replicates

Each trial will last 9 weeks and will involve 9 consenting human volunteers sleeping in huts from dusk to dawn 6 days of each week of the trial. To allow assessment of blood-feeding inhibition, all unused nets will be given 6 holes each measuring 4cmx4cm in accordance with WHO guidelines [9]. Treatments will be rotated each week using a randomised Latin Square Design while sleepers will be rotated daily to control for hut position effect and sleeper attractiveness to mosquitoes respectively. On the 7^th^ day of each week, huts will be cleaned and aired in preparation for the next rotation cycle. The trials will run for a total of 54 nights and replicate nets collected from the field will be rotated between huts on successive nights (one net per night). The efficacy of each ITN hut treatment at each timepoint will be measured in terms of the proportion of mosquitoes dead after 24 h, proportion exiting into the veranda trap and the reduction in blood-feeding relative to the control untreated nets. The intensity of resistance to pyrethroids in the vector population at the hut site and the involvement of mixed function oxidases in pyrethroid resistance will be assessed during each experimental hut trial following standard WHO susceptibility bioassay guidelines [15].

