### Data management and analysis

Household data collected during the census and ITN follow up surveys will be captured on electronic forms using smartphones installed with OpenDataKit (ODK) Collect in Benin and by paper forms in Cameroon and Tanzania. Data from the surveys at 12, 24, and 36 months will be used to calculate attrition, functional survival and median survival time using Kaplan–Meier estimators. For functional survival, nets reported as given away, sold, or stolen will be excluded from the analysis. Negative binomial regression will be used to compare hole surface area between DuraNet® Plus and DuraNet®. Data on WHO bioassays and tunnel tests will be obtained from 30 nets of each product type sampled at each time point. A chi-squared test will be used to assess the proportion of nets of each ITN type passing the WHO criteria for alphacypermethrin and PBO bioefficacy based on combined cone and tunnel tests. Proportional outcomes (mortality, blood-feeding, exophily) from the experimental hut trials will be compared at each time point using mixed effects logistic regression, with huts, sleepers, net replicate and nightly observational error included as random-effects while numerical outcomes (entry) will be compared with negative binomial regression. A separate model will be fitted for each outcome to determine whether there is a significant change in improved mosquito mortality achieved DuraNet® Plus compared to DuraNet® over time and between the three countries. All analysis will be performed on STATA version 17.

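### The hut-trial section gives two incompatible rules for moving field nets between huts and two different counts of field nets

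*Protocol article*

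**What the plan says.** All the text on rotation is in the Experimental hut trials section of the Protocol article. On treatments and sleepers: "Treatments will be rotated each week using a randomised Latin Square Design while sleepers will be rotated daily". On the seventh day of each week, "huts will be cleaned and aired in preparation for the next rotation cycle". On length: "Each trial will last 9 weeks and will involve 9 consenting human volunteers sleeping in huts from dusk to dawn 6 days of each week", and "The trials will run for a total of 54 nights". The same paragraph then says that "replicate nets collected from the field will be rotated between huts on successive nights (one net per night".

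On the number of nets, the section opens with: "Fifty-four (54) DuraNet® Plus and 54 DuraNet® nets from all three countries will be tested together in experimental huts at each annual timepoint". The list of nine treatments that follows gives 54 replicates for each of six field-net treatments (two net types by three countries). It gives 6 replicates each for the untreated net, the new DuraNet and the new DuraNet Plus.

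Table 2, in Bioefficacy studies and chemical analysis, shows 54 nets for hut trials at each of 12, 24 and 36 months, 162 in all. Its heading is "Number of DuraNet® Plus and DuraNet® ITNs to be sampled for laboratory assays, chemical analysis and hut trials at each study site", and the text above it says the counts are for each net type. A footnote to the hut-trial column adds that the trials take place only in Benin, with nets drawn from every site.

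The Data management and analysis section fits mixed logistic models to the proportional hut outcomes, "with huts, sleepers, net replicate and nightly observational error included as random-effects".

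**The concern.** The weekly rule and the nightly rule cannot both be followed for field nets, which make up six of the nine treatments. The Latin square controls hut position only if each treatment stays in its assigned hut for the week. The cleaning day protects the next treatment only if treatments change at that point and not before. A hut team that acted on the nightly sentence would lose both protections for the field nets, and could put a DuraNet net in a hut used the night before by a DuraNet Plus net, or the reverse. That is the comparison on which the hut trial's superiority question rests.

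The two counts differ threefold in the number of distinct nets per country. This affects how many nets each site must withdraw and how many independent nets stand behind each country's estimate. It also affects the model. If each field net is used on one night only, it contributes a single hut-night, and for those nets the net-replicate effect cannot be separated from the nightly error. If each is used on three nights, the two effects can be separated, but 54 hut-nights are then not 54 nets.

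**Working it through.** **Inputs.** From Experimental hut trials: 9 weeks, 6 nights a week, 9 treatments (6 of them field nets), 9 sleepers, cleaning on day 7, and the replicate counts in the list. From Table 2: 54 hut-trial nets per timepoint. The number of huts is not stated. I take it as nine, to match the nine treatments and nine sleepers.

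**The plan's own figures.**
- Nights: 9 × 6 = 54, as stated.
- One net per treatment per night: 54 replicates per field-net treatment, as listed.
- Table 2: 54 × 3 timepoints = 162 per type per site, as stated.
- Untreated and new nets: 6 replicates, one for each night of a six-night week, so each is used on 54 / 6 = 9 nights.

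The last line matters. These three treatments also run for 54 nights but are listed with 6 replicates, so in this list a replicate is a net and not a hut-night. By the same usage, 54 replicates of a field-net treatment means 54 nets.

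**Rotation, weekly rule.** Each hut changes treatment 9 − 1 = 8 times, each time after cleaning. Changes without cleaning: 0.

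**Rotation, nightly rule applied to field nets only.**
- In a 9 × 9 Latin square each hut holds a field-net treatment in 6 of the 9 weeks.
- A six-night week has 6 − 1 = 5 changes with no cleaning between them.
- Per hut: 5 × 6 = 30 uncleaned changes, so 30 / 54 = 56% of nights at most.
- Per trial: 30 × 9 huts = 270. Equivalently, 5 changes × 6 field-net huts in use × 9 weeks = 270.
- If moves were spread evenly over the six field-net treatments (an assumption; the document does not say), 3 of the 5 possible predecessors would be the other product, or 60% of moves.

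**Net count per timepoint.**

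| | Opening sentence, read as a total | Treatment list |
|---|---|---|
| Per type | 54 | 54 × 3 = 162 |
| Both types | 108 | 324 |
| Per type per country | 54 / 3 = 18 | 54 |
| Field hut-nights | 6 × 54 = 324 | 324 |
| Nights per net | 324 / 108 = 3 | 324 / 324 = 1 |

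Under the list each field net is used on one night, so no single net could go from hut to hut on successive nights. The nightly sentence therefore does not fit the list either, unless it refers to the treatment's nets as a group.

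**The case against.** The strongest reply is that this is a slip of wording in a condensed journal article. The explicit rule for treatments is weekly rotation with cleaning. The later sentence speaks of replicate nets and adds that there is one per night. The arithmetic leaves one workable design: a different replicate each night in the hut assigned to the treatment that week. The list gives the net count plainly, the phrase about all three countries can be read as 54 from each, and any reuse of nets would be handled by the net-replicate random effect.

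Most of this stands as a reading of intent, and I accept it as the likely one. It does not remove the contradiction. The article is not silent on the nightly procedure; it states one, and the words say that nets move between huts. Nor does Table 2 fully settle the count. Its heading supports 54 per site, but the footnote on nets from every site leaves room to read 54 as pooled. The random effect would allow for reuse in the model but would not turn 18 nets into 54.

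A reader might also infer that residue would reach the untreated hut and raise control mortality, or that 45 of 54 nights (83%) in a hut would follow a different treatment uncleaned. The document does not support either inference. The nightly sentence covers only nets collected from the field; the untreated and new nets follow the weekly rule with cleaning. The 45 nights (5 × 9) would require all nine treatments to move nightly, which no sentence says. Nor can it be said how far the comparison of DuraNet Plus with DuraNet would shrink: residue would tend to blur a difference, but the document gives no figure for transfer from a net to a hut in one night.

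**Conclusion.** The section contradicts itself on two points that have to be carried out in practice.

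1. Weekly Latin-square rotation with cleaning cannot be combined with nightly movement of field nets between huts. Followed literally among the six field-net treatments, the nightly rule would break the control of hut position and allow up to 30 of 54 nights per hut (270 moves per trial) with an uncleaned change. Some of these would be between DuraNet and DuraNet Plus. The figure assumes nine huts and a different field-net treatment each night; the resulting bias is of unknown size and may be small.
2. The number of field nets per timepoint is 108 under the opening sentence read as a total and 324 under the treatment list. The list is the better supported figure.

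The probable intent is sound, so this is a fault in the stated rules and not evidence of a faulty design. It is worth correcting because the hut trial is where superiority is tested at each annual timepoint, and the correction is cheap.

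**What to change.** Replace the wording on rotation between huts on successive nights with a statement that each treatment stays in its assigned hut for the six nights of a week, that a different replicate field net of that treatment is used each night, and that the treatment moves only after the cleaning day.

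Reconcile the opening sentence with the treatment list and Table 2 as 54 nets of each type from each country, that is 162 of each type and 324 field nets per timepoint. Word the Table 2 footnote so that 54 is clearly the number per site. If 18 nets per country, each reused on three nights, is what is intended, correct the 54 replicates in the list and the hut-trial column of Table 2 instead.

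The cost is two sentences and a footnote. With 54 per country, no huts, nights, sleepers or nets are needed beyond those already in Table 2. The Status of study section reports only the 6-month surveys and bioassays as complete, so on the document's own account the wording can be settled before the 12-month hut trial. If a hut trial has already been run, its report should state how the nets were actually moved and how many distinct nets were used.

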### Data management and analysis

Household data collected during the census and ITN follow up surveys will be captured on electronic forms using smartphones installed with OpenDataKit (ODK) Collect in Benin and by paper forms in Cameroon and Tanzania. Data from the surveys at 12, 24, and 36 months will be used to calculate attrition, functional survival and median survival time using Kaplan–Meier estimators. For functional survival, nets reported as given away, sold, or stolen will be excluded from the analysis. Negative binomial regression will be used to compare hole surface area between DuraNet® Plus and DuraNet®. Data on WHO bioassays and tunnel tests will be obtained from 30 nets of each product type sampled at each time point. A chi-squared test will be used to assess the proportion of nets of each ITN type passing the WHO criteria for alphacypermethrin and PBO bioefficacy based on combined cone and tunnel tests. Proportional outcomes (mortality, blood-feeding, exophily) from the experimental hut trials will be compared at each time point using mixed effects logistic regression, with huts, sleepers, net replicate and nightly observational error included as random-effects while numerical outcomes (entry) will be compared with negative binomial regression. A separate model will be fitted for each outcome to determine whether there is a significant change in improved mosquito mortality achieved DuraNet® Plus compared to DuraNet® over time and between the three countries. All analysis will be performed on STATA version 17.

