### Randomisation, blinding and sample size calculations

Households will be the unit of randomisation of this study. Participating households will be blinded to the type of ITN they received while data collectors will be blinded to the allocation of households to the study arms. Study nets (DuraNet® Plus and DuraNet®) will be identical in appearance. Two cohorts of nets of each ITN type will be followed; cohort 1 to assess ITN survivorship, attrition and Fabric integrity and cohort 2 for nets to be withdrawn for assessment of bioefficacy and insecticide content. A sample size of 510 households per study arm was found sufficient to detect a 7 points difference in ITN functional survival rate over 3 years between households receiving DuraNet® Plus and those receiving DuraNet® with 80% power, assuming a baseline 3-year survival rate of 25%. This sample size was increased by 100 households to account for loss to follow up over time. To account for nets to be withdrawn for bioefficacy studies, hut trials and insecticidal content, an additional 310 households per arm will be included in the study, hence a total of 920 households will be recruited per study arm at each site. It is estimated that about 3 nets will be required per household therefore the study will require 2,760 nets of each ITN type at each study site.

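### Median net survival is to be read from a Kaplan-Meier curve that can drop only around the 12-, 24- and 36-month surveys, so it is biased upward and the gap between arms can vanish or be inflated

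*Protocol article*

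**What the plan says.** Data management and analysis names both the estimator and the data: the "surveys at 12, 24, and 36 months will be used to calculate attrition, functional survival and median survival time using Kaplan–Meier estimators". It mentions neither interpolation nor an interval-censored method.

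Follow-up for ITN attrition measures loss by "recording the physical presence of the net at 6-, 12-, 24- and 36-months post ITN distribution". For a missing net, the article mentions asking why it was lost. It does not mention asking when.

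Follow-up for ITN fabric integrity states that "condition will be observed on all nets of cohort 1 at 6-, 12-, 24- and 36-months post distribution". A net enters the torn category (pHI 643 or more) on the strength of that inspection.

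The sample size paragraph rests on a different quantity. The number of households was judged "sufficient to detect a 7 points difference in ITN functional survival rate over 3 years", with a 25% baseline and 80% power.

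**The concern.** Kaplan-Meier assumes that the failure time is known. Here a net that is functional at 12 months and gone or torn at 24 months failed at some unknown time in between. If the failure is entered at the detecting survey, every failure is recorded late. The curve stays flat between surveys, drops only at them, and first crosses 50% at or near a survey time.

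Two things are at stake. The reported median is longer than the true one. The Discussion says that durability studies serve replacement planning and procurement, where a shift of several months matters. The contrast between arms in medians also becomes unreliable: a real gap can disappear if both medians fall in the same interval, and a small gap can look like a full year if they fall on either side of a survey.

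**Working it through.** **Inputs from the article.** Baseline 3-year functional survival 25%; difference 7 points; 80% power; 510 households per arm before the allowance for loss; surveys at 12, 24 and 36 months in the survival analysis, with a 6-month survey also collected; a median retention of 1.64 years cited in the Background.

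**Assumptions.** The second rate (32%, with 18% as the alternative) and the shape of the survival curve (Weibull, shape k from 1 to 3). The article gives neither.

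**Step 1: the plan's own figure.** "A sample size of 510 households per study arm was found sufficient". With n = (z_α + z_β)² [p₁(1−p₁) + p₂(1−p₂)] / d², 25% vs 32% and a one-sided 5% level:

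(1.645 + 0.842)² × (0.1875 + 0.2176) / 0.07² = 6.183 × 0.4051 / 0.0049 ≈ 511, or 514 with the pooled-variance formula.

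That is close to 510. The pooled formula gives 652 for 25% vs 32% two-sided; for 25% vs 18% it gives 425 one-sided and 540 two-sided. The article states neither level nor sidedness. The match is used here only to choose 32% as the main working value.

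**Step 2: true medians.** Fix the curve at its 36-month value: S(t) = S₃₆^((t/36)^k). The true median is 36 × [ln 2 / (−ln S₃₆)]^(1/k). For k = 1 this is 36 × 0.6931/1.3863 = 18.0 months at 25%, and 36 × 0.6931/1.1394 = 21.9 months at 32%.

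**Step 3: median as planned.** Take the first of 12, 24 and 36 months at which S ≤ 0.5. The last column interpolates linearly between the two surveys on either side of 50%.

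| Shape k | S₃₆ | S(12) | S(24) | True median | Kaplan-Meier | Excess | Interpolated |
|---|---|---|---|---|---|---|---|
| 1 | 25% | 0.630 | 0.397 | 18.0 | 24 | 6.0 | 18.7 |
| 1 | 32% | 0.684 | 0.468 | 21.9 | 24 | 2.1 | 22.2 |
| 1.5 | 25% | 0.766 | 0.470 | 22.7 | 24 | 1.3 | 22.8 |
| 1.5 | 32% | 0.803 | 0.538 | 25.8 | 36 | 10.2 | 26.1 |
| 2 | 25% | 0.857 | 0.540 | 25.5 | 36 | 10.5 | 25.7 |
| 2 | 32% | 0.881 | 0.603 | 28.1 | 36 | 7.9 | 28.4 |

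Interpolation for the first row: 12 + 12 × (0.630 − 0.5)/(0.630 − 0.397) = 18.7. At shape 3 the true medians are 28.6 and 30.5, and Kaplan-Meier gives 36 for both.

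**Step 4: sampling variation.** In 2,000 simulated trials of 510 independent units per arm (25% vs 32%), the two arms had identical Kaplan-Meier medians in 93.5% of trials at shape 1 and 96.4% at shape 2. The true gaps were 3.9 and 2.6 months. The simulation ignores the roughly 3 nets per household, which affects precision but not the bias.

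**Step 5: the quantity the trial was sized on.** In the same simulations the difference in survival at 36 months averaged 7.0 points at both shapes.

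**Step 6: the other direction.** For 25% vs 18%, shape 1 has true medians of 18.0 and 14.6 (Kaplan-Meier 24 and 24), shape 1.5 has 22.7 and 19.7 (24 and 24), and shape 2 has 25.5 and 22.9 (36 and 24). Which cases tie and which are inflated depends on the direction; the upward bias does not.

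**Step 7: the 6-month survey.** Adding it to the grid changes none of these Kaplan-Meier medians, because every true median lies beyond 12 months.

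**Illustration.** The cited 1.64 years is 1.64 × 12 = 19.7 months. A net type with that median would be reported at 24 months.

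**The case against.** The strongest reply is that this does not touch the comparison the trial was built for, and that is right. A reader might infer that the method can hide the difference the trial was sized to detect. The article does not support that: the sizing rests on functional survival over 3 years, 36 months is a survey time, and Kaplan-Meier estimates survival there without this timing bias (Step 5). Functional survival is also a planned output separate from the median.

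Other parts of the reply also stand. Nothing in the article makes the median its headline result; it is the last of three survival outputs in one sentence. The 32% is inferred, and no curve shape is given, so the size of the bias is conditional. Leaving the 6-month survey out of the analysis sentence is a small mismatch with the two follow-up sections, not the cause of the bias.

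It can also be said that the article condenses a fuller protocol, does not say how event times are coded, and that silence on dates of loss does not show that none are collected. With actual visit dates, medians would cluster around the survey windows and not equal 12, 24 or 36 exactly, but failures would still be recorded late. Recalled dates could help for missing nets. They would not help for torn nets, whose status is established by inspection. So this part softens the mechanism without removing it.

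**Conclusion.** The concern holds for the median survival time and for the contrast between arms in medians. As written, the median falls at or near a survey time and is biased upward. With 25% vs 32% at 3 years and Weibull shapes 1 to 2, the excess is 1.3 to 10.5 months. A true gap of 3.9 months can be reported as zero, and one of about 3 months as 12. These sizes depend on the assumed second rate and shapes, and on failures being timed at the detecting survey; the upward direction appeared at every shape tried. The 36-month functional survival comparison, and with it the basis of the sample size, is not affected. This is a correction to one stated output, not a threat to the trial's main physical-durability comparison.

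**What to change.** Keep the survival proportions at each survey and the 36-month comparison between arms. For the medians, define each failure as lying between the last survey at which the net was functional and the first at which it was not. Estimate medians and their confidence intervals from an interval-censored model, such as Weibull interval-censored regression, or by interpolating between surveys. Use all four surveys; the 6-month data are already in hand according to Status of study, and they narrow the interval for early failures.

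In the table above, simple interpolation brings every median to within 0.7 months of the true value. The cost is a change of analysis wording and a standard routine, plus an assumption about how failures are distributed within intervals. No further data or change of sample size is needed. The article reports follow-up as still under way, so the change can be made before the final data.
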